### *Cetuximab (per the package insert)*

- Dose: 400 mg/m^2 cycle 1 day 1 (loading dose), 250 mg/m^2 cycle 1 day 8 & 15, followed by 250 mg/m^2 day 1, 8, and 15 on cycle 2 and subsequent cycles
- Administration: Administer via IV infusion (infusion pump or syringe pump); loading dose over 2 hours, weekly maintenance dose over 1 hour. Do not administer as IV push or bolus. Do not exceed an infusion rate of 10 mg/min. Do not shake or dilute. Administer via infusion pump or syringe pump. Following the infusion, an observation period (1 hour) is recommended; longer observation time (following an infusion reaction) may be required. The maximum infusion rate is 10 mg/minute. Administer through a low protein-binding 0.22 micrometer in-line filter.
- Pre-medication: Premedicate with an H1 antagonist (eg, diphenhydramine) IV 30 to 60 minutes prior to the first dose; premedication for subsequent doses may be necessary based on clinical judgment.
- Route of administration: intravenous
- Starting dose and dose escalation: not applicable
- Dose adjustments/modifications/delays: see Appendix 1

- Duration of therapy: Patients in both the safety run-in and dose expansion stages will continue to receive study therapy until disease progression according to RECIST v1.1, unacceptable toxicity, death, patient or physician decision to withdraw, or pregnancy, whichever occurs first. Criteria in which patients in all cohorts may continue treatment after radiographic progression are detailed in Section 4.1.2.
- Tracking of dose: not applicable

*Pembrolizumab (per the package insert)*

- Dose: 200 mg IV day 1 every 21 days
- Administration: Pembrolizumab 200 mg will be administered as a 30 minute IV infusion every 3 weeks. Sites should make every effort to target infusion timing to be as close to 30 minutes as possible. However, given the variability of infusion pumps from site to site, a window of -5 minutes and +10 minutes is permitted (i.e., infusion time is 30 minutes: -5 min/+10 min). The Pharmacy Manual contains specific instructions for the preparation of the pembrolizumab infusion fluid and administration of infusion solution.
- Pre-medication: none required
- Route of administration: intravenous
- Starting dose and dose escalation: not applicable
- Dose adjustments/modifications/delays: see Appendix 1
- Duration of therapy: Patients in both the safety run-in and dose expansion stages will continue to receive study therapy until disease progression according to RECIST v1.1, unacceptable toxicity, death, patient or physician decision to withdraw, or pregnancy, whichever occurs first. Criteria in which patients in all cohorts may continue treatment after radiographic progression are detailed in Section 4.1.2.
- Tracking of dose: not applicable

### **Dose modifications, interruptions, and delays**

Every effort should be made to administer study products on the planned dose and schedule. In the event of significant toxicity dosing may be delayed and/or reduced as described in Appendix I. In the event of multiple toxicities, dose modification should be based on the worst toxicity observed. Patients are to be instructed to notify Investigators at the first occurrence of any adverse symptom.

### **Medication Errors**

Medication errors may occur in this study, from the administration of the wrong drug, to the wrong patient, at the wrong time, or at the wrong dosage strength. Such medication errors occurring to a study participant are to be captured on the medication error electronic case report form (eCRF) which is a specific version of the adverse event (AE) page, and on the SAE form

when appropriate. In the event of medication dosing error, AGICC and medical monitor should be notified immediately.

Medication errors are reportable irrespective of the presence of an associated AE/SAE, including;

- Medication errors involving patient exposure to evorpaccept (ALX148), cetuximab, and/or pembrolizumab
- Potential medication errors or uses outside of what is foreseen in the protocol that do or do not involve the participating subject.

Whether or not the medication error is accompanied by an AE, as determined by the Investigator, the medication error should be captured on the medication error version of the adverse event (AE) page and, if applicable, any associated adverse event(s) is captured on an adverse event (AE) eCRF page.

## 6.2 STUDY DRUG PREPARATION/HANDLING/STORAGE/ACCOUNTABILITY

### 6.2.1 ACQUISITION AND ACCOUNTABILITY

*Evorpaccept (ALX148)*: ALX Oncology Ltd will provide evorpaccept (ALX148) from investigational supply

*Cetuximab*: Eli Lilly USA, LLC will provide cetuximab from commercial supply

*Pembrolizumab*: Merck & Co, Inc. will provide pembrolizumab from commercial supply

### 6.2.2 FORMULATION, APPEARANCE, PACKAGING, AND LABELING

*Evorpaccept (ALX148)*

The evorpaccept (ALX148) Injection, 20 mg/mL, is packaged in 20 mL (400 mg) and 50 mL (1000 mg) USP Type I clear glass vials with a 20 mm Teflon coated rubber serum stopper and tamper-evident aluminum seal. The formulation is composed of evorpaccept (ALX148) at 20 mg/mL, in 20 mM citrate, 150 mM NaCl, 0.02% (w/v) Polysorbate 80, pH 6.0. Each 20 mL vial (20 mg/mL) contains 400 mg of evorpaccept (ALX148). Each 50 mL vial (20 mg/mL) contains 1000 mg of evorpaccept (ALX148).

*Cetuximab*

Cetuximab injection is a sterile, preservative-free, clear, colorless solution in a 2 mg/mL single-dose vial supplied as follows:

- 100 mg/50 mL individually packaged in a carton (NDC 66733-948-23)

- 200 mg/100 mL individually packaged in a carton (NDC 66733-958-23)

### *Pembrolizumab*

- Pembrolizumab (MK-3475) Solution for Infusion is a sterile, non-pyrogenic aqueous solution supplied in single-use Type I glass vial containing 100 mg/4 mL of pembrolizumab (MK-3475). The product is preservative-free, latex free solution which is essentially free of extraneous particulates.
- Pembrolizumab (MK-3475) Solution for Infusion vials are filled to a target of 4.25mL (106.25mg) to ensure recovery of 4.0mL (100mg).

---

## 6.2.3 PRODUCT STORAGE AND STABILITY

### *Evorpaccept (ALX148)*

Specific storage and stability instructions for evorpaccept (ALX148) are provided in the Pharmacy Manual.

### *Cetuximab*

- Store vials under refrigeration at 2° C to 8° C (36° F to 46° F).
- Do not freeze or shake.
- Increased particulate formation may occur at temperatures at or below 0° C (32° F).
- Discard any remaining solution in the infusion container after 8 hours at controlled room temperature or after 12 hours at 2° C to 8° C.
- Discard any unused portion of the vial.

### *Pembrolizumab*

Pembrolizumab (MK-3475) Solution for Infusion, 100 mg/ 4 mL vial: pembrolizumab (MK-3475) Solution for Infusion vials should be stored at refrigerated conditions 2 – 8 °C (36 - 46 °F) and protected from light. Do not shake and do not freeze. Vials should be stored in the original box to ensure the drug product is protected from light.

---

## 6.2.4 PREPARATION

### *Evorpaccept (ALX148)*

Specific preparation and dispensing instructions for evorpaccept (ALX148) are provided in the Pharmacy Manual.

### *Cetuximab*

Specific preparation and dispensing instructions for cetuximab are provided in the Pharmacy Manual.

*Pembrolizumab*

Specific preparation and dispensing instructions for pembrolizumab are provided in the Pharmacy Manual.

### 6.3 MEASURES TO MINIMIZE BIAS: RANDOMIZATION AND BLINDING

There is no randomization or blinding in this study.

### 6.4 STUDY INTERVENTION COMPLIANCE

All study drugs are given intravenously, therefore a drug diary is not needed. All patients will be given a study calendar detailing study activities.

Subject retention and compliance with the protocol will be reported using:

- A CONSORT diagram illustrating the subject flow through the trial
- Tables summarizing retention and compliance
- Listings showing retention and compliance results at the individual subject level

### 6.5 PROHIBITED THERAPY

Any concomitant therapy intended for the treatment of cancer, whether health authority approved or experimental, is prohibited for various time periods prior to starting study treatment (depending on the anti-cancer agent, see Section 5.2), and during study treatment until disease progression is documented and the patient has discontinued study treatment. This includes but is not limited to chemotherapy, hormonal therapy, immunotherapy, radiotherapy (see exception below), investigational agents, or herbal therapy.

The following medications are prohibited while receiving study treatment, unless otherwise noted:

- Traditional herbal medicines, as their use may result in unanticipated drug-drug interactions that may cause or confound assessment of toxicity. The concurrent use of vitamins is permitted.
- Any live, attenuated vaccine (e.g., FluMist) within 30 days prior to Cycle 1 Day 1 or at any time during the study and for at least 5 months after the last dose of study drug.
- Use of steroids to premedicate patients for whom CT scans with contrast are contraindicated (i.e., patients with contrast allergy or impaired renal clearance). Such patients are allowed on study and MRIs of the chest, abdomen, and pelvis with a non-

contrast CT scan of the anatomical region of interest will be performed for tumor assessment.

- Immunomodulatory agents, including but not limited to interferons or interleukin-2, during the entire study; these agents could potentially increase the risk for autoimmune conditions.
- Immunosuppressive medications, including but not limited to cyclophosphamide, azathioprine, methotrexate, and thalidomide; these agents could potentially alter the activity and the safety of immunotherapy.
- Systemic corticosteroids and tumor necrosis factor- $\alpha$  (TNF- $\alpha$ ) inhibitors may attenuate potential beneficial immunologic effects of treatment. Therefore, in situations where systemic corticosteroids or TNF- $\alpha$  inhibitors would be routinely administered, alternatives, including antihistamines, should be considered first by the treating physician.
- Systemic glucocorticoids for any purpose other than to modulate symptoms from an event of clinical interest of suspected immunologic etiology. The use of physiologic doses of corticosteroids may be approved after consultation with the Sponsor.
- Acute emergency administration, topical applications, inhaled sprays, eye drops, or local injections of corticosteroids are allowed. As noted in Section 5.2 (Exclusion Criteria), the use of systemic steroid therapy or any other form of immunosuppressive therapy is an exclusion criterion for study entry.
- Hematopoietic growth factors should not be administered prophylactically before initial treatment with study drugs. Hematopoietic growth factors and transfusions may be administered according to local guidelines if indicated during the study.

The above lists of medications are not necessarily comprehensive. Thus, the investigator should consult the prescribing information for any concomitant medication as well as online drug interaction resources when determining whether a certain medication is metabolized by or strongly inhibits or induces CYP. In addition, the investigator should contact the Medical Monitor if questions arise regarding medications not listed above.

There are no prohibited therapies during the Post-Treatment Follow-up Phase.

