24. Final study / treatment discontinuation visit: At least 28 days and no more than 35 days after discontinuation of treatment, patients will return to undergo the listed activities (unless already completed in the last week, or last 6 weeks for response assessment). Patients continuing to experience toxicity at this point following discontinuation of treatment will continue to be followed at least every 4 weeks until resolution or determination, in the clinical judgment of the Investigator, that no further improvement is expected. If the patient has any concern and contacts the clinic, the patient will be seen in the clinic within 5 calendar days of the patient’s contact with the clinic (assessments will be the same as the assessments performed at the Final Study/Treatment Discontinuation Visit).

25. Overall survival information will be collected via telephone calls and/or clinic visits every 3 months  $\pm 14$  days (first call and/or clinic visit to occur 3 months following the Final Study/Treatment Discontinuation Visit) until death, withdrawal of consent, the patient is lost to follow-up, study termination by AGICC, or a maximum of 2 years from the Final Study/Treatment Discontinuation Visit.

26. Blood will be drawn for pharmacokinetic (PK) analysis prior to the start of evorpaccept (ALX148) infusion and immediately following completion of evorpaccept (ALX148) infusion (within 6 minutes after end of infusion) on Day 1 of Cycles 1-5. Starting with Cycle 6, the frequency of the pre- and post-evorpaccept (ALX148) infusion PK draws will be decreased to every 3 cycles (i.e. C6D1, C9D1, C12D1, etc). A final blood draw for PK analysis will be performed at the Final Study Visit / Treatment Discontinuation Visit. In addition to samples collected at the scheduled times, an additional blood sample may be requested from patients experiencing unexpected and/or serious AE’s with the date and time documented in the eCRF. Additional details can be found in the Laboratory Manual and Section 8.2.6.

27. Blood will be drawn for pharmacodynamic (PD)/biomarker analyses prior to the start of evorpaccept (ALX148) infusion at Day 1 of each cycle and at the Final Study Visit/Treatment Discontinuation Visit. Additional details can be found in the Laboratory Manual and Section 8.2.6.

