28. AEs due to prior cancer therapies that have not returned to  $\leq$ Grade 1 or baseline. Participants with endocrine-related AEs Grade  $\leq$ 2 that are now controlled with treatment/hormonal therapy are eligible.

Exclusion criteria based on infectious diseases:

29. Active infection requiring IV antibiotics at screening.

30. Patients with active hepatitis B (chronic or acute). Active hepatitis B infection is defined as having a positive hepatitis B surface antigen [HBsAg] test at screening. Patients with a cleared hepatitis B infection (as defined by the presence of hepatitis B core antibody [anti-HBc], absence of HBsAg, and negative HBV DNA) are eligible.
31. Patients with active hepatitis C. Patients positive for hepatitis C virus (HCV) antibody are eligible only if polymerase chain reaction (PCR) is negative for HCV RNA.
32. Known HIV infection.
33. Recent COVID-19 diagnosis (symptomatic or asymptomatic). To become eligible (following symptomatic infection), the patient must not have fever for 24 hours (without using medicine to reduce fever), other symptoms have improved, and at least 10 days have passed since onset of symptoms. To become eligible (following asymptomatic infection, ie positive test only), at least 10 days have passed since the positive test. In either case, a repeat COVID-19 test is not required. Likewise, a persistently positive test (if obtained) does not continue to exclude the patient should the other criteria be satisfied.
34. Influenza vaccination should be given during influenza season. Patients must not receive live, attenuated influenza vaccine (e.g., FluMist®) within 30 days prior to Cycle 1 Day 1 or at any time during the study and for at least 5 months after the last dose of study drug.

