#### **8.2.4 FINAL STUDY/TREATMENT DISCONTINUATION VISIT**

A final study visit is required if patients come off study for any reason. At least 28 days and no more than 35 days after discontinuation of treatment, patients will return to undergo the activities listed in Schedule of Events (Section 1.3), unless the assessment(s) were already completed within the prior week, or the last 6 weeks for the tumor response assessment.

Patients continuing to experience toxicity at this point following discontinuation of treatment will continue to be followed at least every 4 weeks until resolution or determination, in the clinical judgment of the Investigator, that no further improvement is expected. If the patient has any concern and contacts the clinic, the patient will be seen in the clinic within 5 calendar days of the patient’s contact with the clinic (assessments will be the same as the assessments performed at the Final Study/Treatment Discontinuation Visit).

---

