#### **8.2.5 AFTER TREATMENT / SURVIVAL FOLLOW-UP**

Overall survival information will be collected via telephone calls and/or clinic visits every 3 months  $\pm$ 14 days (first call and/or clinic visit to occur 3 months following the Final Study/Treatment Discontinuation Visit) until death, withdrawal of consent, the patient is lost to follow-up, study termination by AGICC, or a maximum of 2 years from the Final Study/Treatment Discontinuation Visit.

---

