| Grade 4 thrombocytopenia (Platelet count <25,000/mm  )                                        | Platelets count ≥50,000/mm                         | Decrease 1 dose level | Same dose levels (2 nd occurrence: reduce cetuximab 1 dose level) |

- a. Hematologic toxicities should be managed via supportive care (including transfusions) by Investigators' medical judgement.
- b. A treatment delay of more than 14 days (beyond the next scheduled study drug infusion) due to lack of recovery will result in discontinuation of the patient from the treatment unless otherwise agreed between the Investigator and AGICC.
- c. Dose reduction of evorpaccept (ALX148) by 1 and, if needed, 2 dose levels will be allowed depending on the type and severity of toxicity encountered. Patients requiring more than 2 dose reductions will be discontinued from the treatment and entered into the follow-up phase, unless otherwise agreed between the Investigator and AGICC.

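### Section 6.5 bans live, attenuated vaccines for at least 5 months after the last dose, then says without exception that nothing is prohibited in post-treatment follow-up

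*Protocol*

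**What the plan says.** Section 6.5 of the protocol contains three relevant statements.

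- The list of prohibited medications opens: "The following medications are prohibited while receiving study treatment, unless otherwise noted".
- One item on the list is any live, attenuated vaccine. It is barred in the 30 days before Cycle 1 Day 1 and then "at any time during the study and for at least 5 months after the last dose of study drug".
- The section closes: "There are no prohibited therapies during the Post-Treatment Follow-up Phase".

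The vaccine rule appears once more, in exclusion criterion 34 of Section 5.2: "Patients must not receive live, attenuated influenza vaccine". The time limits are the same, but that criterion covers influenza vaccine only.

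No section defines when the Post-Treatment Follow-up Phase starts. Three places bear on it:

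- A footnote to the neutropenia and thrombocytopenia table in Section 12.1.3 says that patients needing more than two evorpacept dose reductions "will be discontinued from the treatment and entered into the follow-up phase", unless otherwise agreed.
- Section 8.2.4 sets the final visit: "At least 28 days and no more than 35 days after discontinuation of treatment, patients will return to undergo the activities" in the schedule.
- Section 8.2.5 sets the first survival contact: "first call and/or clinic visit to occur 3 months following the Final Study/Treatment Discontinuation Visit", with a window of 14 days either side.

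**The concern.** The vaccine item is written to outlast treatment, because its 5-month clock runs from the last dose. The closing sentence covers that same period and says nothing is prohibited in it. A site asking what a patient may receive after treatment would naturally go to the one sentence in Section 6.5 that names the phase. Followed literally, it would permit a live vaccine that the bullet above forbids.

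What is at stake is patient protection and uniform conduct across the roughly five sites (Section 5.5), not the statistics. For live influenza vaccine, exclusion criterion 34 is a second safeguard. For every other live vaccine, the Section 6.5 bullet is the only statement of the ban. Recording would not reliably catch an error either: under Section 6.6, concomitant medications are captured only until 30 days after treatment discontinuation, so a vaccine given in months 2 to 5 would usually go unrecorded.

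**Working it through.** The plan gives no figure to reproduce. The check compares the texts and then asks whether the two periods overlap.

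**Do the texts conflict?**

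| Rule (Section 6.5) | Applies to | Period | Exception stated |
|---|---|---|---|
| Vaccine item | any live, attenuated vaccine | until at least 5 months after last dose | none |
| Closing sentence | all therapies | Post-Treatment Follow-up Phase | none |

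The words allowing for items that note otherwise belong to the list heading. They let the vaccine item extend beyond treatment, but they do not qualify the closing sentence, which is separate and comes later. The section is titled Prohibited Therapy and places vaccines under that title, so the closing sentence covers them.

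**Do the periods overlap?**

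Inputs:
- ban: at least 5 months after last dose (Section 6.5), about 5 × 30.44 = 152 days;
- final visit: day 28 to 35 after discontinuation (Section 8.2.4; Section 1.3, footnote 24);
- first survival contact: 3 months (about 91 days) ± 14 days after the final visit (Section 8.2.5).

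Assumption: discontinuation falls on the day of the last dose. If discontinuation is dated later, each overlap shrinks by that gap.

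Formula: overlap = length of ban − start day of follow-up.

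1. Start at discontinuation: 152 − 0 = 152 days, the whole ban.
2. Start at the final visit: 152 − 28 = 124 days; 152 − 35 = 117 days.
3. Start at the first survival contact: earliest day 28 + 91 − 14 = 105, latest day 35 + 91 + 14 = 140. Overlap 152 − 105 = 47 days down to 152 − 140 = 12 days.

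With 30-day months the ban is 150 days and the first two cases give 150 days and 115 to 122 days (77% to 81% of the ban).

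The third case is a limit rather than a likely reading, since the first survival call is a contact made within follow-up, not its beginning. Under the first two readings the conflict lasts about 4 to 5 months.

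**The case against.** The best defence is that a specific rule overrides a general one. The vaccine item has its own clock, which would serve no purpose unless it continued after treatment. The closing sentence can be read as a default that mainly tells sites the ban on other anticancer treatment has ended, in line with the section's opening paragraph. The wording leans slightly that way: the opening and closing statements speak of therapy, while the list speaks of medications. Many readers would settle the matter like this, which is why the point is minor. But the protocol states no such order of precedence, and the section title covers both terms.

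Three further points have some force.

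- Exclusion criterion 34 repeats the ban for live influenza vaccine, and Section 6.6 names only inactive influenza vaccination among its permitted examples. That narrows the gap to other live vaccines without closing it.
- The Section 12.1.3 footnote concerns only patients needing more than two dose reductions and does not use the full name of the phase. It therefore supports a start at discontinuation without fixing one for all patients.
- The vaccine item gives no rationale. That it protects patients is an inference, though a reasonable one.

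None of these makes the two sentences compatible as written.

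**Conclusion.** The point holds as a minor correction. Section 6.5 contradicts itself for live, attenuated vaccines given during follow-up within 5 months of the last dose. The conflict spans about 117 to 152 days on the natural readings of when follow-up begins, and at least 12 days on the latest start considered. These figures rest on a phase start that the protocol leaves undefined and on treating discontinuation as the last dose; the existence of an overlap does not depend on which of these starts is chosen. The practical gap is for live vaccines other than influenza. Response rate, progression-free survival, power and error rates are not affected.

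**What to change.** Keep the closing sentence of Section 6.5 and add an exception: *except that the ban on live, attenuated vaccines set out above continues for its full minimum of 5 months from the last dose.* This restores the evident intent of the vaccine item and works whatever date follow-up is taken to begin.

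The cost is one clause in the next amendment. Visits, data collection and analysis do not change.
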